Current interventions for myopia prevention remain limited. One of the most widely recognized preventive strategies is increasing outdoor activity [10–12]. However, the growing reliance on electronic devices and increasing academic demands have substantially reduced the time that children and adolescents spend outdoors. Although atropine has been used as a pharmacological intervention for myopia prevention [13–15], further research is required to determine its optimal dosage and appropriate target population. Recently, various types of functional lenses have been developed for myopia management. These lenses incorporate different mechanisms for myopia control, such as inducing peripheral myopic defocus [16] or higher-order aberrations [17,18]. However, most studies have focused on children who are already myopic. Whether these technologies can prevent myopia in children who have not yet developed it warrants further investigation.

We developed an aberration-enhanced dual-surface (AEDS) lens by combining two techniques that have been shown to be effective in myopia control—peripheral myopic defocus and aberration enhancement—which were incorporated into the anterior and posterior surface design of the lens, respectively. We plan to conduct a randomized controlled trial involving emmetropic and mildly hyperopic children to evaluate its effectiveness in preventing myopia.

1. **Hypothesis**

Hypothesis 1: AEDS lenses can effectively prevent the onset of myopia in non-myopic children.

Hypothesis 2: The effectiveness of AEDS lenses in preventing myopia in emmetropic children will be greater than that in mildly hyperopic children.

1. **Study objectives**

Primary objective: To evaluate the effectiveness of AEDS spectacle lenses in preventing myopia in non-myopic children.

Secondary objective: To examine the influence of baseline characteristics and daily behaviours on the effectiveness of AEDS spectacle lenses.

1. **Material and methods**

**6.1 Study design**

This study will be a 2-year, single-centre, double-masked, randomized controlled trial commencing in June 2023. Participants will be randomly assigned to either the intervention group or the control group and further stratified as emmetropic (−0.50 D < cycloplegic spherical equivalent refraction [SER] < +0.50 D) or mildly hyperopic (+0.50 D ≤ cycloplegic SER ≤ +2.00 D). Participants in the intervention group will wear AEDS lenses in their daily lives, whereas those in the control group will wear single-vision (SV) lenses.

- 1. **Scheme**

**Figure 1. Study flow diagram**

[figure not shown]

- 1. **Enrolment and eligibility**

Participants will be recruited from the hospital outpatient clinics. Advertisements will be displayed in the hospital’s public areas, and referrals from clinical optometrists will form part of the recruitment strategy.

Inclusion criteria: (1) age 6–12 years; (2) SER between −0.50 D and +2.00 D measured using an autorefractor under cycloplegia; (3) cycloplegic astigmatism ≤ 1.50 D; (4) distance best-corrected visual acuity (BCVA) of 0.1 logMAR or better; (5) anisometropia ≤ 1.50 D; (6) willingness to wear spectacle lenses.

Exclusion criteria: (1) intraocular pressure ≥ 21 mmHg; (2) manifest strabismus; (3) ocular or systemic diseases affecting visual development (excluding refractive errors); (4) history of ocular or systemic surgery affecting visual development; (5) use of defocus spectacle lenses or low-concentration atropine eye drops within the past 3 months; (6) use of orthokeratology lenses or other products intended to prevent or control myopia within the past 6 months (e.g., red light–based treatment methods); (7) history of systemic medications affecting growth and development (e.g., growth hormone); (8) concurrent participation in any clinical trial related to myopia control or prevention; (9) any other condition deemed unsuitable for participation by the investigator.

- 1. **Sample size**

The sample size was calculated using a two-sample t-test assuming equal variances in SPSS (IBM Corp., Armonk, NY, USA). The mean (standard deviation) annual axial elongation was assumed to be 0.36 (0.23) mm in the control group, based on previous studies of non-myopic children aged 6–12 years [13–15,19]. The intervention effect of the AEDS lens was assumed to be 40%. Allowing for a dropout rate of 10%, a minimum sample size of 94 participants (47 per group) was required to achieve 80% power at a two-sided significance level of 0.05.

- 1. **Randomisation and masking**

Randomisation will be conducted by a clinical research coordinator. Eligible participants will be randomly assigned in a 1:1 ratio to either the intervention group or the control group according to a computer-generated allocation sequence. The coordinator will notify the manufacturer of the appropriate lens type for each participant and will inspect the lenses upon receipt. All spectacle lenses will be packaged in identical eyeglass cases and provided by the coordinator to the dispensers, who will distribute them to the participants. The clinical research coordinator will not be involved in recruitment, clinical examinations, data collection, or data analysis. All other investigators (including examiners, dispensers, and statisticians), as well as participants and their parents or guardians, will remain masked throughout the study. To objectively assess whether blinding was inadvertently compromised, a formal evaluation will be conducted at the end of the study. Participants (or their guardians) and the primary outcome assessors will be asked to guess the assigned group. Statistical analysis will then be performed to determine whether the proportion of correct guesses differs significantly from that expected by chance (50%). The results of this blinding assessment will be presented in the final research report.

- 1. **Interventions**

Participants in the intervention group will wear AEDS spectacle lenses, whereas participants in the control group will wear SV spectacle lenses. The AEDS lens (Shanghai Baoli Lai Optical Lens Co. and Suzhou Mingshi Optical Technology Co., Ltd.) was designed by combining two technologies: a concentric microlens array on the anterior surface to generate peripheral myopic defocus, and a radial refractive gradient on the posterior surface to increase total ocular aberrations. The design is protected under the Patent Cooperation Treaty (202122046858X and 202221884655.6). Both the anterior and posterior surfaces of the lens incorporate a central optical zone (10.13 mm in diameter) designed to correct refractive error and provide a clear retinal image at the foveal centre. The peripheral zone of the anterior surface contains 11 concentric circular microlens arrays with different refractive powers, and the radius of the outermost ring is 59.57 mm. The refractive power of the lenslets is +5.00 D in the three inner rings, +5.50 D in the intermediate four rings, and +6.00 D in the four outer rings. The peripheral zone of the posterior surface incorporates a radial refractive gradient designed to enhance higher-order aberrations (e.g., spherical aberration and secondary astigmatism).

The following equation describes the Zernike polynomial representation of aberration-enhanced modulation on the posterior surface of the AEDS lens:

$$z=\frac{cr^{2}}{1+\sqrt{1-{(1+k)c}^{2}r^{2}}}+\sum_{i=1}^{N} 2\pi A_{i}Z_{i}(\rho,\varphi)$$

where z denotes the sagittal height of the surface, c is the vertex curvature, r represents the radial distance from the optical axis, k denotes the conic constant of the surface, N is the number of Zernike coefficients included in the series, i is the index of the Zernike polynomial term, ρ is the normalised radial coordinate, and φ is the angular coordinate. The normalised orthogonal polynomials expressed in polar coordinates are presented in Table 1, where x = ρcosφ, y = ρsinφ, ρ^2^ = x^2^ + y^2^, and n denotes the order of the polynomial.

**Table 1. Normalised orthogonal polynomials in polar coordinates**

| n | i | $Z_{i}(\rho,\varphi)$ |
| --- | --- | --- |
| 0 | 1 | 1 |
| 1 | 2 | $2\rho\cos\varphi$ |
| 1 | 3 | $2\rho\sin\varphi$ |
| 2 | 4 | $\sqrt{3}(2\rho^{2}-1)$ |
| 2 | 5 | $\sqrt{6}\rho^{2}\sin2\varphi$ |
| 2 | 6 | $\sqrt{6}\rho^{2}\cos2\varphi$ |
| 3 | 7 | $\sqrt{8}(3\rho^{3}-2\rho)\sin\varphi$ |
| 3 | 8 | $\sqrt{8}(3\rho^{3}-2\rho)\cos\varphi$ |
| 3 | 9 | $\sqrt{8}\rho^{3}\sin3\varphi$ |
| 3 | 10 | $\sqrt{8}\rho^{3}\cos3\varphi$ |
| 4 | 11 | $\sqrt{5}(6\rho^{4}-{6\rho}^{2}+1)$ |
| 4 | 12 | $\sqrt{10}(4\rho^{4}-{3\rho}^{2})\cos2\varphi$ |
| 4 | 13 | $\sqrt{10}(4\rho^{4}-{3\rho}^{2})\sin2\varphi$ |
| 4 | 14 | $\sqrt{10}\rho^{4}\cos4\varphi$ |
| 4 | 15 | $\sqrt{10}4\rho^{4}\sin4\varphi$ |
| ...... | ...... | ...... |

The following equation represents the Zernike polynomial corresponding to a selected configuration of the posterior surface. The magnitudes of the different aberrations at 10° and 15° field-of-view angles are presented in Table 2.

$$z= \frac{{cr}^{2}}{1+\sqrt{1-(1+k)c^{2}r^{2}}}+2\pi(2.3993Z_{1}-1.0182Z_{2}-0.0605Z_{3}+2.4179Z_{4}-0.2798Z_{5}-0.0062Z_{6}-0.2999Z_{7}-0.0170Z_{8}+0.0268Z_{9}+0.1145Z_{10}+0.0245Z_{11}-0.0332Z_{12}-0.0098Z_{13}+0.0626Z_{14}+0.0027Z_{15})$$

**6.8 Study visit schedule**

Participants will undergo 24 months of follow-up during the trial. Table 3 presents the follow-up schedule and the examinations to be performed at each visit.

**Table 3. Examinations at baseline and at each follow-up visit**

| **Items** | **Baseline** | **1 month** | **3 months** | **6 months** | **9 months** | **12 months** | **15 months** | **18 months** | **21 months** | **24 months** |
| --- | --- | --- | --- | --- | --- | --- | --- | --- | --- | --- |
| Inclusion/exclusion criteria assessment | √ |  |  |  |  |  |  |  |  |  |
| Informed consent | √ |  |  |  |  |  |  |  |  |  |
| Slit-lamp biomicroscopy | √ |  |  | √ |  | √ |  | √ |  | √ |
| Subjective and objective refraction without cycloplegia | √ |  | √ | √ | √ | √ | √ | √ | √ | √ |
| Subjective and objective refraction with cycloplegia | √ |  |  | √ |  | √ |  | √ |  | √ |
| Monocular pupillary distance | √ |  | √ | √ | √ | √ | √ | √ | √ | √ |
| Spectacle lens dispensing | √ |  |  |  |  |  |  |  |  |  |
| Frame adjustment and pupil height measurement | √ | √ | √ | √ | √ | √ | √ | √ | √ | √ |
| Best-corrected visual acuity | √ |  | √ | √ | √ | √ | √ | √ | √ | √ |
| Intraocular pressure | √ |  |  |  |  | √ |  |  |  | √ |
| Strabismus at 33 cm | √ |  |  |  |  | √ |  |  |  | √ |
| Pupil size | √ |  |  |  |  | √ |  |  |  | √ |
| Axial length | √ | √ | √ | √ | √ | √ | √ | √ | √ | √ |
| Accommodative amplitude | √ |  |  |  |  | √ |  |  |  | √ |
| Accommodative facility | √ |  |  |  |  | √ |  |  |  | √ |
| Contrast sensitivity | √ |  |  | √ |  | √ |  |  |  | √ |
| Daily lens-wearing time |  | √ | √ | √ | √ | √ | √ | √ | √ | √ |
| Questionnaire on daily schedule |  | √ | √ | √ | √ | √ | √ | √ | √ | √ |
| Questionnaire on lens adaptation | √ | √ | √ |  |  |  |  |  |  |  |

**6.9 Outcome measurements**

Distance visual acuity will be measured, with and without spectacles, using a standard logarithmic visual acuity chart at a distance of 5 m. BCVA will be assessed after correction of the subjective refractive error.

Objective and subjective SER, both with and without cycloplegia, will be measured by a masked examiner. One drop of 0.5% proxymetacaine hydrochloride and three drops of 1% cyclopentolate will be administered to induce cycloplegia, with a 5-minute interval between each instillation. Refractive error will be measured at least 30 minutes after the administration of the eye drops to ensure complete cycloplegia, confirmed by pupil dilation (> 6 mm), absence of the light reflex, and lack of an accommodative response. Objective refractive error will then be measured using an autorefractor (Topcon KR-800, Topcon Corporation, Tokyo, Japan), and the averaged value (including total astigmatism) will be calculated as the mean of ten consecutive measurements. Subjective SER will be measured using a phoropter (Topcon Corporation, Tokyo, Japan). Lenses will be replaced if the change in subjective SER exceeds 0.25 D or if there are scratches on the lens surface.

Mean AL and corneal astigmatism will be calculated as the average of five consecutive measurements obtained using an IOLMaster (Carl Zeiss Meditec, Jena, Germany).

Participants’ daily schedules and subjective experiences while wearing the lenses will be recorded using self-administered questionnaires (Table S1 in Additional file 2), which consist of items on lens-wearing duration (Items 1–2), daily schedule (Items 3–8), and adaptation to the lenses (Items 9–10). The average daily lens-wearing time over 12 months (T12) and 24 months (T24) will be calculated using the following formulae:

*T_12_ = (**a_1_ × 30 + a_2_× 60 + a_3_ × 90 + a_4_ × 90 + a_5_ × 90)/360*

*T_24_ =0.5× [T_12_+(a_6_ + a_7_ + a_8_ + a_9_)* *× 90/360]*

In these equations, *a_1_* to *a_9_* represent the average daily lens-wearing time reported at each follow-up visit (from 1 month to 24 months). *T_12_* represents the average daily lens-wearing time over the first 12 months, and *T_24_* represents the average daily lens-wearing time over 24 months.

The average daily lens-wearing time at each visit will be calculated using the following formula:

*Average daily lens-wearing time at each visit = (b × d_1_ + c × d_2_)/(d_1_+d_2_)*

In this equation, *b* denotes the average daily lens-wearing time on workdays, whereas *c* denotes the average daily lens-wearing time on weekends or holidays, both reported at each visit. *d_1_* and *d_2_* represent the total number of workdays and weekends (or holidays), respectively, between the current follow-up visit and the previous visit. The average daily hours spent on outdoor activities, electronic device use, and sleep will also be calculated using a similar formula.

1. **Data management**

The study will use paper-based documentation for data collection. Each participant will be assigned a unique screening identifier to facilitate accurate data retrieval and tracking. In compliance with national regulations, all study documents and publications will be encrypted or de-identified to safeguard participant confidentiality.

Data from each follow-up visit must be entered into the data collection system within seven days to ensure timely and accurate data management. After the 12-month follow-up visit, outcome data and group allocation will be provided to the data analysts for an interim analysis, following removal of identifiable information, to assess the preliminary efficacy and safety of the AEDS lens. Masking will be maintained for data collectors and participants. After completion of the 2-year follow-up, data managers will perform comprehensive logical checks, and all identified discrepancies will be resolved before database lock. Once the data collection system has been locked, the final version of the data management report will be generated. All data will be reviewed by the principal investigator, sponsor, statisticians, and monitors under masked conditions. The dataset will then be transferred to the statistical team for formal analysis in accordance with the pre-specified statistical analysis plan.

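### Section 7 releases group allocation to the data analysts at 12 months, although Section 6.5 keeps statisticians masked throughout and provides for no unmasked analyst

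*Protocol*

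**What the plan says.** Protocol Section 6.5 (Randomisation and masking) gives the allocation to one person, the clinical research coordinator, and keeps that person out of the analysis: "The clinical research coordinator will not be involved in recruitment, clinical examinations, data collection, or data analysis". For everyone else it says: "All other investigators (including examiners, dispensers, and statisticians), as well as participants and their parents or guardians, will remain masked throughout the study".

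Section 7 (Data management) describes a different arrangement from month 12 onward. It states that after the 12-month visit "outcome data and group allocation will be provided to the data analysts for an interim analysis". What is stripped out first is identifying information, and the purpose is given in the same sentence: "following removal of identifiable information, to assess the preliminary efficacy and safety of the AEDS lens". The next sentence limits who stays masked: "Masking will be maintained for data collectors and participants".

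For the end of the 2-year follow-up, the same section says: "All data will be reviewed by the principal investigator, sponsor, statisticians, and monitors under masked conditions". The data then go to the final analysis: "The dataset will then be transferred to the statistical team for formal analysis in accordance with the pre-specified statistical analysis plan".

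**The concern.** The trial is labelled double-masked in Section 6.1, and Section 6.5 makes masked statisticians an explicit promise. A report that repeats this promise would be inaccurate if Section 7 is followed as written.

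What is at stake is the independence of analysis decisions from the data. Section 8 names subgroups by age and by daily lens-wearing time without cut-offs. It calls for both adjusted and unadjusted comparisons without saying which one leads. If such choices are still open at month 12, people who have seen the effect by group could settle them.

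The end-of-study masking check in Section 6.5 would not show the problem. It asks participants or guardians and the primary outcome assessors to guess the group, and it does not ask analysts.

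**Working it through.** No figure in the plan bears on this point, so the check compares the statements role by role.

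| Role | Section 6.5 | Section 7, from month 12 |
| --- | --- | --- |
| Clinical research coordinator | Knows allocation, barred from analysis | Not mentioned |
| Examiners, data collectors | Masked throughout | Masked |
| Participants | Masked throughout | Masked |
| Parents or guardians, dispensers | Masked throughout | Not listed |
| Statisticians | Masked throughout | Not listed after the interim, yet masked at the final review |
| Data analysts (interim) | No such role; masked if they count as investigators or statisticians | Receive outcomes and allocation |

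1. **Who may analyse unmasked under Section 6.5?** One person knows allocation, and that person may not analyse data. All other investigators are masked. The number of unmasked analytic roles is therefore zero.
2. **Who analyses unmasked under Section 7?** The data analysts, from the 12-month release. Only identifying information is removed, and no coding of the group label is mentioned. Listing only collectors and participants as still masked points the same way: the analysts are not expected to be.
3. **Do steps 1 and 2 agree?** Not unless the analysts fall outside all other investigators and are not statisticians, or the allocation is supplied under a neutral code. The protocol says neither.
4. **Does the final masked review conflict too?** Section 7 uses three terms: data analysts (interim), statisticians (masked review) and statistical team (final analysis). If the first two overlap, the review by statisticians is not masked. If they are separate people and the result is kept from the reviewers, it can be. The protocol does not say which applies, so this second conflict is conditional.
5. **What analysis freedom remains?** Section 8 fixes the model type and the full covariate list, and Section 6.1 fixes the refractive strata. The age and wear-time cut-offs, and whether the adjusted or unadjusted result leads, are not fixed in the protocol. They may be fixed in the statistical analysis plan, which is not at hand and whose date relative to the interim is unknown.
6. **How much follow-up lies after the release?** At most 24 − 12 = 12 of 24 months, or 4 of the 9 follow-up visits in Table 3 (15, 18, 21 and 24 months). This is an upper limit per child. If the release waits for the last child's 12-month visit, children enrolled earlier will already have passed some of these visits. It counts schedule exposure and does not measure bias.

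**The case against.** The strongest defence is that data analysts and statisticians are different words and may mean different people. A firewalled interim team, or labels supplied as A and B, would reconcile most of the text. The formal analysis is also said to follow a pre-specified plan, which may already settle the cut-offs and the lead analysis. Outcome measurement is protected on paper: collectors and participants stay masked, refraction is done by a masked examiner, and axial length and autorefraction are averages of repeated instrument readings (Section 6.9). No stopping or adaptation rule is tied to the interim.

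Much of this stands, and it limits the point. It does not remove it: the protocol states neither a separate team nor coded labels, and even a separate team needs an exception that Section 6.5 does not contain. An analysis plan could define the team, but it could not make the two protocol sections agree.

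A reader might infer more than the document supports:

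- **That the masked final review is certainly false.** It is false only if the interim analysts take part in it or its members see the interim result.
- **That the covariates are open to choice.** Section 8 names them all.
- **That the interim uses uncleaned data.** Section 7 schedules comprehensive checks after 2 years. It does not say that nothing is checked earlier, and it requires data entry within seven days of each visit.
- **That nothing limits who sees the interim result.** The stated recipients are the data analysts, and collectors and participants are to stay masked. What is missing is an express rule on circulating group-level results.
- **That second-year measurements are biased.** Those visits are made by collectors who are stated to stay masked, and a group-level result does not reveal a given child's lens.

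**Conclusion.** The concern holds as an internal contradiction about analyst masking, and it should be fixed. Section 6.5 allows no unmasked analyst, and Section 7 creates one at month 12. The statement that statisticians are masked throughout therefore does not hold as written.

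This rests on two readings: that those who analyse the trial data count among the investigators or statisticians of Section 6.5, and that group allocation means the actual allocation and not a code. The further conflict with the masked final review depends on whether the interim analysts are a separate team.

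The consequence is a risk to analysis decisions and data review after month 12, and it applies only to choices not already fixed in an analysis plan finalised before the release. The document gives no basis for a size of bias. It does not show that outcome assessment is compromised.

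**What to change.** - **Release.** Either the coordinator releases the 12-month data with coded group labels (A/B) only, or the protocol names a separate interim analyst who takes no part in the masked review or the final analysis. The second option suits an interim whose purpose is to judge the AEDS lens by name, because a coded comparison must be decoded before anyone can read it that way.
- **Sign-off.** Finalise the 24-month statistical analysis plan before the release, including the age and wear-time cut-offs and which of the adjusted and unadjusted analyses leads. This is needed under either option, since A/B labels still show the size of the difference between groups.
- **Circulation.** State that group-level interim results are not shared with examiners, dispensers, families or the masked reviewers before database lock. Section 7 describes the masked review after the lock, so for its members the restriction should run until that review is finished.
- **Wording.** Make Sections 6.5 and 7 agree. With coded labels, Section 6.5 can stand and Section 7 changes. With a separate analyst, Section 6.5 must name the exception and Section 7 must list everyone who stays masked.
- **If allocation has already been released.** Report the date and the roles that were unmasked, and correct the masking statements accordingly, including the one on the final review if those people take part in it.

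The cost is a change of wording, minor extra data handling at month 12, and restricted circulation of the interim results. Holding back publication of 12-month results until the last visit would go further, but that is a preference and the point does not depend on it.
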